### Study objectives

2.1

The study has one primary and four secondary objectives (**Figure 1**). The primary objective is to evaluate the spatial and quantitative correlations between OE and BOLD MRI measurements of hypoxia and [^18^F]MISO values of uptake in the tumour once before patients receive surgery and once prior to commencement of chemoradiation treatment. The secondary objectives are: 1) to evaluate the repeatability of the MRI biomarkers of hypoxia by means of test-retest scans acquired prior to patients commencement of chemoradiation treatment; 2) to develop a framework to integrate image-derived tumour hypoxia information into radiation treatment plans and estimate the potential clinical benefits of this approach compared to conventional radiation treatment; 3) to evaluate the ability of MRI biomarkers of hypoxia to assess tumour response to chemoradiation treatment; 4) to evaluate whether changes in the MRI biomarker of hypoxia observed during chemoradiation treatment are predictive of patient overall survival. Secondary objectives 3 and 4 of this study are exploratory.

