#### Primary objective

2.3.1

Spatial correlation between hypoxic tumour volume (HTV) determined with MRI and [^18^F]MISO will be evaluated via measurements of Dice similarity coefficient. Dice similarity coefficients > 0.75 will be considered a good spatial correlation. Quantitative correlation of voxel-wise and HTV-average levels of hypoxia will be evaluated via measurement of the Pearson’s correlation coefficient. Correlation coefficients > 0.7 will be considered a strong correlation (27).

#### Secondary objective 1

2.3.2

Repeatability of voxel-wise and HTV-average levels of hypoxia in the tumour, calculated as explained below for each hypoxia imaging biomarker, will be assessed via measurements of intraclass correlation coefficient (ICC). Repeatability is considered excellent, good, moderate or poor for ICC values > 0.9, 0.75-0.9, 0.5- 0.75 and< 0.5, respectively. Additionally, similarity between the HTV defined with the MRI biomarker at the two timepoints will be assessed via calculation of Dice similarity coefficient. Dice similarity coefficients > 0.9 will be considered a strong correlation.

#### Secondary objective 2

2.3.3

The predicted patient benefits of the hypoxia-guided dose-painting radiotherapy plan will be compared with the actual patient outcomes following conventional treatment, by using metrics including modelled tumour control probability (TCP) and toxicity measurement to organs at risks and healthy brain (including equivalent uniform dose). Voxel-wise dose-painting prescriptions within the conventional radiotherapy targets will be escalated from 60 Gy based on the level of hypoxia determined by the selected MRI imaging biomarker according to the method previously described by Toma-Dasu et al. (28). Targets delineation and constraints to organs at risk as per ESTRO-EANO guidelines (29) will be set equally for the optimisation of the conventional and dose-painting plans. Success for this objective will be achieved if the dose-painting plans result in improved TCP by more than 15% over conventional treatment, while dose metrics to organs at risk remain similar.

#### Secondary objective 3

2.3.4

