**Figure 4 f4:**
[figure not shown]
Example of quantitative images obtained from MRI protocol acquisition on a healthy volunteer.

A region of interest (ROI) will be delineated with a semi-automated tool and checked by an experienced neuroradiologist on the T_2_-weighted image as the hyperintense regions around the tumour. The ROI will be propagated to the T_1_, T_2_, T_2_
^*^ and CBF maps. Voxel-wise and median values of R_1_, R_2_, R_2_
^*^ and CBF within the ROI will be calculated from the quantitative T_1_, T_2_, T_2_
^*^ and CBF maps, respectively. The reproducibility, repeatability and accuracy of the quantitative-MRI protocol will also be assessed using guidelines and a phantom developed by the National Institute of Standards and Technology and the International Society of Magnetic Resonance in Medicine (42).

On one hand, HTV will be defined via OE MRI as the proportion of voxels within the ROI being refractory in R_1_ for O_2_ challenge [i.e. ▵R_1_ ≤ 0, where ▵R_1_ = R_1_ (O_2_) – R_1_ (air)] and well-perfused (i.e. CBF > 0), as previously determined by experts in the field (36, 41, 43, 44). ▵R_1_ will be calculated in two ways. First, it will be calculated from the R_1_ maps obtained from the T_1_-mapping sequences acquired before [R_1_ (air)] and during O_2_ breathing [R_1_ (O_2_)]. Second, it will be calculated from T_1_ maps derived from the T_1_-weighted dynamic acquisition, such that R_1_ (air) is derived from the average of the first two R_1_ maps acquired at baseline while breathing air and R_1_ (O_2_) is derived from the last four R_1_ map acquired during oxygen breathing. ▵R_1_ values obtained with the two approaches will be compared. The approach which will provide the most reliable ▵R_1_ values in the test-retest scan across the entire patient cohort will then be selected to calculate the HTV. Voxel-wise ΔR_1_ values in the HTV will be converted into values of partial pressure of oxygen (pO_2_) using a similar approach to the one used by Chakhoyan et al. (35), which exploits known values of pO_2_ in normal appearing white and gray matter and uses these values to calibrate the pO_2_ values in the tumour. This approach will provide a way to quantitatively measure voxel-wise levels of hypoxia.

On the other hand, HTV will be defined via BOLD MRI by using a previously established method to estimate relative oxygen extraction fraction (rOEF) in human gliomas from T_2_, T_2_

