## Discussion

3

This diagnostic/prognostic imaging study will enable validation of the role of non-invasive MRI biomarkers of hypoxia that could be used to improve diagnosis, radiation treatment, prognosis and treatment response assessment of GBM patients. This study is ambitious in that it aims to characterise the evolution of tumour hypoxia levels during the whole course of patient management pipeline, with a plan to acquire MRI and PET/CT scans pre-operatively at diagnosis, prior to commencement of chemoradiation treatment, 12 weeks following completion of radiotherapy and at suspected diagnosis of recurrence, and supplementary MRI scans in a test-retest setting prior to commencement of radiotherapy and during radiotherapy. The supplementary MRI scans, which are required to test hypothesis for secondary objectives 1 and 4, will be considered optional based on patients’ status and compliance. Similarly, patients will be invited for repeat OE/BOLD MRI and [^18^F]MISO PET/CT scans only in case of suspected recurrence on long term MRI surveillance, meaning that there might only be a subset of patients whose data will be used to test hypothesis of secondary objective 3. Nonetheless, this study will generate a large amount of longitudinal multimodal MRI and PET imaging data that will be extremely valuable to unveil important dynamic changes in tumour physiology that currently limit treatment efficacy, thereby providing a means to develop more effective, personalised treatment strategies.

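### For OE MRI, the same test-retest scans choose the ΔR1 method and then judge its repeatability, which raises the chance of an 'excellent' verdict

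*Protocol article*

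**What the plan says.** Section 2.7.2 (MRI analysis) derives ΔR1 once from the static T1 maps and once from the T1-weighted dynamic series. The choice between them is left to the data: "The approach which will provide the most reliable" ΔR1 values in the "test-retest scan across the entire patient cohort will then be selected to calculate the HTV". The section names no reliability metric.

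Secondary objective 1 (section 2.1) assesses repeatability "by means of test-retest scans acquired prior to patients commencement of chemoradiation treatment". Section 2.2 states the hypothesis that repeatability is excellent. Section 2.3.2 applies the ICC to voxel-wise and HTV-average hypoxia levels, "calculated as explained below for each hypoxia imaging biomarker", and grades it as follows: "Repeatability is considered excellent, good, moderate or poor for ICC values > 0.9, 0.75-0.9, 0.5- 0.75 and< 0.5, respectively". It adds a Dice coefficient between the two retest HTVs.

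For OE MRI, the hypoxia level is a pO2 value converted from ΔR1 within the HTV that ΔR1 defines, so the graded biomarker is built on the selected method.

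The Discussion adds: "The supplementary MRI scans, which are required to test hypothesis for secondary objectives 1 and 4, will be considered optional". Section 2.4 likewise makes these scans depend on the patient's willingness.

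**The concern.** When two candidates compete on a noisy measure and the winner is scored on the same data, part of its score is the luck that made it win. Here the contest is about test-retest reliability, and so is the score. The verdict turns on whether a point estimate exceeds 0.9, so a small upward push can change the category.

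Objective 1 has a stated hypothesis and a fixed grading scale, and section 2.1 reserves the label exploratory for objectives 3 and 4. An unearned excellent grade would give OE MRI more support for radiotherapy planning and response assessment than the data warrant. The optional retest scan means the sample for this step may be smaller than the 20 patients planned.

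**Working it through.** **1. Is it the same data?** Sections 2.1 and 2.4 describe one test-retest set, before chemoradiation. Section 2.7.2 uses it across the whole cohort to choose, and section 2.3.2 uses it to grade. No hold-out, second retest set or cross-validation is described. The phantom work in section 2.7.2 checks the MRI protocol and does not choose the method.

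**2. Is there a figure in the plan to reproduce?** None for this step. The sample size of 19 in section 2.10 concerns the primary correlation and is not disputed. The statement there for objective 1 (specificity of at least 85% with 95% certainty) rests on a cited source, cannot be re-derived from the document and does not mention the selection.

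**3. Bound by hand.** Let p be the chance that one pre-specified method gives an ICC above 0.9. With two equally good, positively dependent methods, the chance that the better one does so lies between p and 1 − (1 − p)².
- p = 0.17: upper bound 1 − 0.83² = 0.31.
- p = 0.50: upper bound 1 − 0.50² = 0.75.

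**4. Simulation.** From the plan: up to 20 patients, two scans each, two methods, bar 0.9. Assumed, because the document gives none of them: the true ICCs, the between-method error correlation (0, 0.5, 0.8), a patient signal shared by both methods, and n = 12 as a reduced sample. With signal variance 1, the error variance is (1 − ICC)/ICC. The estimate is the one-way ICC = (MSB − MSW)/(MSB + MSW), where MSB and MSW are the between- and within-patient mean squares. The larger of the two is kept. There were 40,000 runs per scenario. Ranges run over the error correlations, highest correlation first; n = 12 ranges also include variation between repeated runs.

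| n | True ICCs | P(ICC > 0.9), method fixed | P(ICC > 0.9), better of two |
|---|---|---|---|
| 20 | 0.85, 0.85 | 17% | 24–29% |
| 12 | 0.85, 0.85 | 23–24% | 32–38% |
| 20 | 0.90, 0.90 | 50% | 60–67% |
| 20 | 0.85, 0.80 | 17% | 18–20% |
| 20 | 0.85, 0.70 | 17% | 17–18% |

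**5. Mean ICC at n = 20, equal methods.** The selected ICC exceeds that of a pre-specified method by:
- 0.026–0.046 at true ICC 0.75
- 0.017–0.028 at 0.85
- 0.011–0.019 at 0.90

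Against the true ICC, the net bias over these scenarios is only +0.002 to +0.028. The one-way estimator itself runs low: its mean is about 0.837 when the truth is 0.85. At n = 12 and true ICC 0.85, the net bias is about 0.00 to +0.014, no larger than at n = 20.

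**6. Sensitivity.** If the two methods' patient values correlate at only 0.5 and their errors are independent, the n = 20 figures reach 31% (true ICC 0.85) and 73% (true ICC 0.90). The largest mean gain is then 0.056 and the largest net bias 0.038, both at true ICC 0.75.

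**The case against.** Several points on the other side stand.

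- **Scope.** A reader might infer that the whole of objective 1 is affected. It is not. BOLD rOEF has a single definition, so only the OE ICC and OE retest Dice are involved.
- **Bias against truth.** A reader might infer that the reported ICC will be clearly too high, and more so with fewer patients. The calculations do not support this. Net bias is small and does not grow at n = 12. What grows is the difference from a pre-specified method and the chance of passing 0.9.
- **Equal methods are close to the worst case.** With true ICCs of 0.85 and 0.70 the effect is almost nil. The protocol plans the comparison without saying which method is better, so near-equality cannot be excluded.
- **Correlated errors.** Section 2.7.2 calculates the dynamic T1 maps from the static ones, so the two methods' errors probably correlate. The lower ends of the ranges are then more plausible than the upper ends.
- **Different quantities.** Selection is on ΔR1 with an unnamed metric, whereas the endpoint is pO2 in the HTV. The simulation selects on the very ICC it reports, with one value per patient. It is therefore an upper case for the HTV-average ICC and does not model the voxel-wise ICC. A different metric weakens the effect but does not remove it if it tracks retest agreement.
- **Cohort wording.** The reference to the entire cohort most naturally means one choice for all patients, and the Discussion discloses that the scans are optional. This calls for clarification and is not an error in itself.
- **Level of detail.** The article says the two sets of ΔR1 values will be compared, and tabulating both ICCs could be left to a fuller document. The selection rule itself, however, is stated here and draws on the evaluation data.

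**Conclusion.** The point holds for OE MRI. One set of test-retest scans selects the ΔR1 method and then decides whether repeatability is excellent. Relative to a method fixed in advance, the chance of that verdict rises by about 7 to 12 percentage points with 20 patients if both methods have true ICC 0.85, and by about 10 to 17 points if both have 0.90. The mean ICC rises by about 0.01 to 0.05 relative to a fixed method, for true ICCs of 0.75 to 0.90. These figures rest on two similarly good methods, a shared patient signal, error correlation from 0 to 0.8, and selection on the reported ICC. The consequence is modest and matters mainly when the true ICC is near 0.9. It is worth correcting because the remedy is cheap and the objective is judged against a fixed bar.

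**What to change.** Choose one of two routes before the retest data are examined.

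1. **Name one ΔR1 method as primary** and treat the other as a sensitivity analysis. No correction is then needed.
2. **Keep the data-driven choice**, but name the selection metric and report the ICC and retest Dice of both approaches. Judge the selected OE biomarker against 0.9 with an estimate and confidence interval that repeat the selection step, by a patient-level bootstrap or leave-one-patient-out selection. Because the small-sample ICC already runs low, show the uncorrected ICCs alongside so that the adjustment is visible.

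Under either route, state that the analysis uses the patients who have a retest scan, and report their number.

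The cost is a little more analysis, with no extra scans or patients. Route 2 gives a slightly less favourable OE ICC. Route 1 gives up the chance of using whichever method proves more repeatable.

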Spatial correlation between HTV after completion of chemoradiation treatment and volume of recurrent tumour at relapse evaluated with standard anatomical imaging will be evaluated via measurements of Dice similarity coefficient. Dice similarity coefficients > 0.9 will be considered a strong spatial correlation. Correlation between the percentage of HTV after completion of chemoradiation treatment and clinical outcome will be evaluated by means of hazard ratio obtained from Cox regression. A hazard ratio > 1 (p<0.05) will indicate that the HTV at suspected recurrence is associated with worse patient overall survival.

#### Secondary objective 4

2.3.5

Correlation between the percentage change of HTV during treatment and patient clinical outcome will be evaluated by means of hazard ratio obtained from Cox regression. A hazard ratio > 1 (p<0.05) will indicate that the increase in HTV during treatment is associated with worse patient overall survival. Given the known prognostic role of sex and age on GBM overall survival (30–32), sub-analyses assessing whether HTV increase during treatment has a sex/age-specific impact on overall survival will be performed.

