^*^ and CBV maps (37). Briefly, the transverse relaxation due to local magnetic field inhomogeneities in a blood vessel network, 
$R_{2}^{'}$
, will be calculated within the ROI from T_2_ and T_2_
^*^ maps according to Equation 1:

(1)
$$R_{2}^{'}=R_{2}^{*}-R_{2}=\left(\frac{1}{T_{2}^{*}}-\frac{1}{T_{2}}\right)$$

Then, the Yablonskiy and Haacke model will be applied to derive the oxygen extraction fraction (OEF) according to Equation 2:

(2)
$$OEF=\frac{R_{2}^{'}}{\zeta \cdot \gamma \cdot \frac{4}{3}\cdot \pi \cdot \Delta \chi \cdot B_{0}}$$

where 
ζ
 is the venous fraction of the blood network and approximately equals the venous blood volume (~0.75.CBV), 
$B_{0}$
 is the magnetic field strength, 
γ
 is the gyromagnetic ratio of value 2.675 . 10^8^ s^-1^ T^-1^, 
△χ
 is the susceptibility difference between deoxygenated and oxygenated blood 
$△\chi =△\chi_{0}\cdot Hct=0.924\cdot 10^{-7}$
, which is calculated from the susceptibility difference between fully deoxygenated and fully oxygenated hemoglobin 
$△\chi_{0}=0.264\cdot 10^{-6}$
 and the small-vessel hematocrit (Hct = 0.35). As the absolute quantification of venous CBV in patients is not feasible, the venous blood vessel fraction 
ζ
 is approximated by CBV and the remaining factors are grouped into a constant 
$c=\gamma \cdot \frac{4}{3}\cdot \pi \cdot △\chi \cdot B_{0}=317\;s^{-1}$
. Using these simplifications, rOEF can be calculated according to Equation 3:

(3)
$$rOEF=\frac{R_{2}^{'}}{CBV\cdot c}=\left(\frac{1}{T_{2}^{*}}-\frac{1}{T_{2}}\right)\cdot \frac{1}{CBV\cdot c}$$

To derive the HTV, a hypoxia rOEF threshold (rOEF_hypoxia_) will be defined from the mean, rOEF_mean_, and the standard deviation, rOEF_SD_, of the tissue within the ROI, such that rOEF_hypoxia_ = rOEF_mean_ + rOEF_SD_. Finally, the HTV will be defined by all voxels within the ROI for which rOEF> rOEF_hypoxia_. Hypoxia levels in voxels belonging to the HTV will be measured by rOEF values.

To facilitate the assessment of spatial and quantitative voxel-wise correlations in HTV and in levels of tumour hypoxia defined by the different imaging biomarkers, all MRI images will be resampled into the spatial resolution of the MRI image with the highest resolution by linear interpolation of voxel-wise intensity values.

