#### PET imaging analysis

2.7.4

PET data will be reconstructed with CT data acquired simultaneously. To quantify the radioactivity concentrations in the PET images as standardised uptake values (SUV), raw PET images will be decay corrected to the point of tracer injection using a fluorine-18 half-life of 109.77 min. PET images will be co-registered to the MRI images acquired at the same timepoint of the study via rigid co-registration of the simultaneously acquired CT image to the T_2_ map. This way the ROI delineated on the T_2_ image can be applied to the PET SUV image and be used for quantification of lesion [^18^F]MISO uptake. The primary measures to quantify lesion [^18^F]MISO uptake will be maximum standardised uptake value (SUV_max_) and tumour-to-background ratios (TBR). TBR images will be derived by normalisation of the SUV image by the mean SUV value calculated in a region of interest delineated in the contralateral healthy brain. The HTV will be defined by all voxels within the tumour ROI with a TBR ≥ 1.2 - threshold value shown to optimally distinguish hypoxic tumour from normoxic brain tissue at 90 min post tracer injection in a previous GBM study (45) – and DSC MRI-derived CBF>0 – indicating well-perfused tissue. Hypoxia levels in voxels belonging to the HTV will be measured by values of pO_2_ derived from TBR values using the above mentioned approach used by Chakhoyan et al. (35).

Finally, to facilitate the assessment of spatial and quantitative voxel-wise correlations in HTV and in levels of tumour hypoxia defined by the different imaging biomarkers, [^18^F]MISO TBR images will be resampled into the spatial resolution of the MRI image with the highest resolution by linear interpolation of voxel-wise intensity values.

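### The BOLD hypoxic volume uses a cut-off taken from the same ROI it classifies, so its size is a poor measure of how much of the tumour is hypoxic

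*Protocol article*

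**What the plan says.** The protocol article defines three versions of HTV, and they are not anchored in the same way.

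- **BOLD (2.7.2, MRI analysis).** The threshold is built from the mean and standard deviation "of the tissue within the ROI, such that rOEF_hypoxia_ = rOEF_mean_ + rOEF_SD", and then "the HTV will be defined by all voxels within the ROI for which rOEF> rOEF_hypoxia". No perfusion condition is stated. Equation 3 obtains rOEF by dividing by CBV.
- **PET (2.7.4, PET imaging analysis).** "The HTV will be defined by all voxels within the tumour ROI with a TBR ≥ 1.2", where TBR comes from "normalisation of the SUV image by the mean SUV value calculated in a region of interest delineated in the contralateral healthy brain". The voxel must also have "DSC MRI-derived CBF>0".
- **OE (2.7.2).** "HTV will be defined via OE MRI as the proportion of voxels within the ROI being refractory in R_1_ for O_2_ challenge", that is ΔR1 ≤ 0, again with CBF > 0.

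These volumes are used in two ways. Section 2.3.1 compares MRI with PET by overlap: "Dice similarity coefficients > 0.75 will be considered a good spatial correlation". Sections 2.3.4 and 2.3.5 put HTV size into Cox models for overall survival, first as a percentage after chemoradiation and then as a change: "Correlation between the percentage change of HTV during treatment and patient clinical outcome".

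**The concern.** PET and OE apply a cut-off that does not depend on the values inside the tumour ROI, so their HTV can run from none to all of it. The BOLD cut-off moves with the tumour. If rOEF rises everywhere, the mean and SD rise with it and the same voxels are flagged.

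Three things are at stake. BOLD could rank voxels well and still miss the primary overlap criterion because its volume is the wrong size. A survival model using BOLD HTV size would relate outcome mostly to the shape of the rOEF histogram, or to ROI size, rather than to hypoxia burden. And with CBV in the denominator and no mask, poorly perfused voxels (cavity, necrosis) could set the threshold themselves.

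**Working it through.** The protocol gives no figure for the share of the ROI that the BOLD rule flags and no rOEF distribution. The rule, the 1.2 TBR and 0.75 Dice criteria and the expected PET volumes are the protocol's. **Every distribution below is an assumption.**

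**1. Invariance (exact).** Replace rOEF by a + b·rOEF with b > 0. The threshold becomes a + b·(mean + SD), so the same voxels exceed it. As a contrast, fix an external threshold that starts at a 15.9% share. If all voxels rise by 0.5, 1 or 2 SD, the external share becomes 30.9%, 50.0% or 84.1%. The ROI rule stays at 15.9%.

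**2. Share flagged for a single-peaked histogram, P(X > mean + SD).** Normal 15.9%; gamma with shape 4, 15.1%; lognormal with sigma 0.5, 13.5%; uniform 21.1%. A very skewed lognormal (sigma 1.0) gives 9.1%.

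**3. Share flagged for a mixture.** Let normoxic voxels be N(0,1), hypoxic voxels N(D,1), and the true hypoxic share p. Then mean = pD, SD = √(1 + p(1−p)D²) and t = mean + SD. Flagged share = p[1−Φ(t−D)] + (1−p)[1−Φ(t)].

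Example with D = 3, p = 0.5: mean 1.5, SD = √3.25 = 1.803, t = 3.303. Hypoxic voxels flagged = 0.5 × [1−Φ(0.303)] = 0.1905; normoxic voxels flagged = 0.0002; total 19.1%. If the truly hypoxic voxels are the PET HTV, attained Dice = 2 × 0.1905/(0.1908 + 0.5) = 0.55.

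| True share p | Flagged, D = 3 | Dice, D = 3 | Flagged, D = 4 | Dice, D = 4 |
|---|---|---|---|---|
| 0% | 15.9% | 0 | 15.9% | 0 |
| 5% | 13.2% | 0.52 | 11.0% | 0.62 |
| 10% | 13.6% | 0.77 | 12.0% | 0.89 |
| 20% | 17.2% | 0.86 | 18.4% | 0.94 |
| 30% | 20.0% | 0.79 | 22.9% | 0.86 |
| 50% | 19.1% | 0.55 | 20.3% | 0.58 |
| 80% | 13.4% | 0.29 | 11.1% | 0.24 |
| 100% | 15.9% | 0.27 | 15.9% | 0.27 |

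Above about half the ROI, more hypoxia gives a smaller BOLD HTV, until it returns to 15.9% at 100%. For D from 1 to 4 and true shares of 2% to 80%, the correlation of flagged with true share runs from 0.35 to −0.12.

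**4. Dice ceiling.** With BOLD share q and PET share f, maximum Dice = 2·min(q, f)/(q + f). With q = 0.159:
- f = 5%: 2 × 0.05/0.209 = 0.48
- f = 30%: 2 × 0.159/0.459 = 0.69
- f = 50%: 2 × 0.159/0.659 = 0.48
- f = 80%: 2 × 0.159/0.959 = 0.33

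For this fixed q, Dice > 0.75 needs f between 0.6q = 9.5% and q/0.6 = 26.5%. The Discussion expects PET HTV of 0.1 to 129.3 cm³, median 12.85 cm³. Dividing each by 0.265 and 0.095 gives the ROI volume needed: about 49 to 135 cm³ at the median, but 0.4 to 1.05 cm³ and 489 to 1358 cm³ at the extremes.

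**5. Low CBV.** Assume 5% of voxels have reduced CBV and the rest are lognormal around the typical value. When the reduced CBV is 10% of typical or less, about 5% of the ROI is flagged and 90% or more of that is low-CBV voxels. At 30% of typical, about 8% to 11% is flagged and roughly 40% to 60% of it is low-CBV.

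**The case against.** Several points on the other side stand.

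- A reader might infer that the rule flags the same share whatever the true hypoxia. That is exact only for shift and scale. The share depends on histogram shape: with strongly bimodal rOEF (D = 10) it follows the truth up to about 30% (10%, 20% and 29.7% flagged at true shares of 10%, 20% and 30%), then reverses to 1.3% at 80%.
- A reader might infer that BOLD cannot meet the Dice criterion. It can: the table shows 0.77 to 0.94 at true shares of 10% to 30%. The 9.5% to 26.5% window holds only if the BOLD share is pinned at 15.9%. The protocol gives PET volumes but no ROI volumes, so the number of patients outside the workable range is unknown.
- A reader might infer that BOLD is uninformative for objectives 3 and 4. The location of the highest-rOEF voxels still bears on overlap with recurrence. HTV-average rOEF still moves with the level of rOEF, and OE HTV is untouched by the self-reference. The denominator of the HTV percentage in section 2.3.4 is not stated. In cm³, BOLD HTV is roughly 0.16 times ROI volume and carries ROI size. Both objectives are labelled exploratory.
- The sample size rests on a Pearson correlation of 0.7, not on Dice, and the Dice criterion is a descriptive label. Imaging data are kept, so another threshold could be applied later.
- The rOEF method is cited as established, and its source is not available here. Precedent for estimating rOEF does not by itself make this threshold suitable for overlap with a fixed-threshold PET volume or for tracking change.

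These points narrow the consequences. They do not remove the mismatch between one self-referenced HTV and two that are not.

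**Conclusion.** The concern holds for the **size** of BOLD HTV. The invariance to shift and scale is exact. Under the assumed unimodal or moderately bimodal distributions (separation up to 4 SD), the flagged share is about 11% to 23%, is about 16% at both extremes of hypoxia, and falls as true hypoxia rises above about half the ROI. As a share of the ROI, BOLD HTV and its change are therefore poor measures of hypoxia burden in the Cox models; as a volume, the change mostly follows ROI size.

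For the primary overlap criterion the effect is conditional: Dice is capped when the PET share is well outside about 10% to 30% of the ROI. The missing perfusion condition is a separate inconsistency with OE and PET. It can make near-zero-CBV voxels nearly all of the BOLD HTV, but how often depends on CBV values that the protocol does not give. Because BOLD HTV feeds a primary outcome measure, the rule should be settled before analysis.

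**What to change.** Before analysis, amend section 2.7.2 as follows.

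1. Take the primary rOEF threshold from contralateral normal-appearing tissue on the same scan, with a prespecified multiplier that flags few normal voxels, for example mean + 2 SD.
2. Apply the CBF > 0 mask already used for OE and PET, plus a prespecified CBV floor, before computing the threshold. CBF > 0 alone removes only zero or negative values, not the near-zero CBV values that inflate rOEF.
3. Report the ROI mean + SD version as a sensitivity analysis.

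The multiplier matters. If normal tissue is normally distributed, + 1 SD flags 15.9% of it and + 2 SD flags 2.3%. In the D = 3 model, with contralateral tissue distributed like normoxic tumour, + 2 SD flags 0.841p + 0.0228(1−p). At p = 10% that is 0.0841 + 0.0205 = 0.1046, so Dice = 2 × 0.0841/(0.1046 + 0.10) = 0.82, against 0.57 with contralateral + 1 SD and 0.77 with the ROI rule. At p = 50%, + 2 SD gives 2 × 0.4207/(0.4321 + 0.5) = 0.90 against 0.55 with the ROI rule. Moving to contralateral tissue while keeping + 1 SD would thus lower Dice at small hypoxic shares.

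Cost: analysis wording and some processing, with no new scan or patient. A contralateral region is already needed for TBR, but rOEF must also be computed there. The primary threshold departs from the one the protocol now states, which is why that version stays as a sensitivity analysis. The CBV floor needs a value that the documents do not supply.

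### The BOLD hypoxic volume divides by CBV but has no perfusion condition, so low-CBV voxels can displace hypoxic ones; and CBF > 0 is a weak perfusion test, mainly for OE MRI

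*Protocol article*

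**What the plan says.** Three HTV definitions feed the primary Dice comparison (section 2.3.1, good if above 0.75).

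- **OE MRI (2.7.2):** ΔR1 ≤ 0 and "well-perfused (i.e. CBF > 0), as previously determined by experts in the field".
- **PET (2.7.4):** TBR ≥ 1.2 and "DSC MRI-derived CBF>0 – indicating well-perfused tissue".
- **BOLD MRI (2.7.2):** Equation 3 gives rOEF = R2'/(CBV·c), where the venous fraction "is approximated by CBV and the remaining factors are grouped into a constant". The cut-off is "rOEF_hypoxia_ = rOEF_mean_ + rOEF_SD", taken over the ROI, and "Finally, the HTV will be defined by all voxels within the ROI for which rOEF> rOEF_hypoxia". No CBF or CBV condition is stated.

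The ROI is drawn on the T2-weighted "image as the hyperintense regions around the tumour", with a semi-automated tool and a neuroradiologist's check. One of the two primary-objective scans falls 3-4 weeks after surgery (2.4). Section 2.7.1 says the DSC perfusion data will be important in the MRI/PET analysis, to find hypoxia that is not due to poor perfusion.

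**The concern.** A ratio with blood volume in the denominator becomes unstable where blood volume is small, and a T2-hyperintense region can contain such tissue: necrosis, oedema if its CBV is low and, after surgery, any cavity left inside the contour. These voxels can do damage twice. They can exceed the cut-off themselves, and they raise the ROI mean and SD that set it.

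The perfusion condition that would limit this is written for the two definitions that do not divide by CBV and is absent from the one that does. The purpose given for DSC in 2.7.1 is thus not carried through to BOLD.

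At stake is the interpretation of the primary endpoint: a low BOLD-PET Dice could mean that BOLD does not see hypoxia, or only that Equation 3 marked low blood volume. The HTV also enters secondary objectives 3 and 4, and the MRI hypoxia level drives the modelled plans in objective 2. Effects there were not computed.

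**Working it through.** **Figures in the plan.** N = 19 for r = 0.7, 98% power and two-sided 5% reproduces with the point biserial model: noncentrality √n·r/√(1−r²), df n−2, power 98.03% (97.4% at N = 18). This point does not alter it. The constant works out as c = 2.675·10⁸ × 4π/3 × 0.924·10⁻⁷ × 3 T = 310.6 s⁻¹, against the printed 317. As a common factor it cancels in the comparison of rOEF with mean + SD, so it plays no part here.

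**Break-even.** A low-CBV voxel outranks a hypoxic one when its R2'/CBV is larger. Assume a hypoxic voxel with OEF 0.60 and CBV 3.5%:

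- Its R2' is 0.60 × 0.035 × 317 = 6.66 s⁻¹.
- A voxel at CBV 0.5% overtakes it once R2' exceeds 0.60 × 0.005 × 317 = 0.95 s⁻¹.
- At CBV 0.2% the figure is 0.38 s⁻¹; at CBV 2% it is 3.80 s⁻¹.
- At CBV 0.5%, R2' = 2 gives rOEF 2/(0.005 × 317) = 1.26, and R2' = 5 gives 3.15.

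**Simulation of Equation 3 with the mean + SD rule.** All tissue and noise values are assumptions. Dice here is against the truly hypoxic voxels, not against PET.

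*Mix A:* 20% hypoxic voxels with R2' doubled, other tissue R2' 4 s⁻¹ (SD 0.8), normal CBV 3%, 10% low-CBV voxels.

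| Low-CBV voxels | Dice, no mask | Dice, CBV floor at 60% of normal |
|---|---|---|
| none | 0.89 | – |
| CBV 0.5%, R2' 0 | 0.78 | 0.87 |
| CBV 0.5%, R2' 1 | 0.66 | 0.87 |
| CBV 0.5%, R2' 2 | 0.25 | 0.87 |
| CBV 0.5%, R2' 4 | 0.00 | 0.87 |
| CBV 1%, R2' 4 | 0.36 | 0.87 |

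A wider set, with 5-20% low-CBV voxels at CBV 0.5-1%, gave 0.00 to 1.00 unmasked and 0.81 to 1.00 with a floor.

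*Mix B:* hypoxic 15% of the ROI (CBV 3.5%, OEF 0.60), viable non-hypoxic tumour (CBV 4%, OEF 0.35), oedema CBV 1.5-2%, necrosis or cavity CBV 0.2-0.5% with R2' 0-5 s⁻¹.

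- *CBV noise SD 0.4%, necrosis 2% or 15% of the ROI (24 scenarios):* the cut-off rises to between 1.9 and 43, against a hypoxic value of 0.60. Dice is 0.00 in all 24 as written, 0.00-0.01 with a cut at zero, and 0.33-0.68 with a CBV > 1% floor.
- *Low noise (CBV SD 0.1%, R2' SD 0.5), necrosis CBV 0.5%:* unmasked Dice is 0.91 (necrosis 15%) or 0.97 (2%) at R2' = 0; 0.00 or 0.75 at R2' = 2; 0.00 in both at R2' = 5.
- *Oedema without necrosis:* at CBV 2%, Dice is 0.66-0.67 with or without a mask; at CBV 1.5%, 0.01-0.23 unmasked.

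**The CBF > 0 condition.** If the CBF estimate carries signed Gaussian noise, the share of voxels passing is Φ(true flow/noise SD): 50% at zero flow, 69% at 0.5 SD, 84% at 1 SD, 98% at 2 SD. If the software returns only non-negative values, just exact zeros are removed. For OE, a voxel with no true ΔR1 satisfies ΔR1 ≤ 0 half the time by symmetry. If the two errors are independent, a voxel with no flow and no response enters the OE HTV with probability 0.5 × 0.5 = 25% under signed noise, or 50% where CBF is always positive.

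**The case against.** **The size rests on values the article does not give.** R2' is in the numerator, so if it falls along with CBV the ratio need not grow. With 20% hypoxic voxels, baseline R2' 3 s⁻¹, R2' noise SD 0.5 and 10% low-CBV voxels, 6% of hypoxic voxels are flagged when low-CBV tissue keeps the full normal R2', 61% at half of it, and 80-82% at 0-10% of it. This stands: near-total displacement is one end of a range. The benign end is not secured either. It needs R2' near 0 and CBV noise small relative to the CBV itself. R2' is a difference between two separately acquired maps whose longest echoes, from Table 1, are 16 × 10 = 160 ms for T2 and 6 + 11 × 5 = 61 ms for T2*, so long relaxation times in fluid are weakly determined.

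**The ROI may already leave out cavity and CSF.** A neuroradiologist checks it, and contouring detail can sit in the full protocol. Inclusion of the cavity is an inference from the T2-hyperintense definition. The rOEF method is also only summarised from a cited source that may mask. Still, the article states an exact voxel rule for all three HTVs, with a perfusion condition on two and none on the third.

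**PET is protected.** TBR ≥ 1.2 must also hold, so a weak CBF condition does not by itself admit unperfused voxels. This stands.

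**The CBF condition may do more than it appears to.** The CBF estimator and noise masking of the named software are not described, and the cut is attributed to cited work. With signed noise it would drop half of the truly unperfused voxels. This too stands, but a cut at zero still does not establish what the text claims for it, "indicating well-perfused tissue".

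**Conclusion.** The point holds as a defect in a primary-endpoint definition whose size is conditional. BOLD is the only HTV that divides by CBV and the only one with no perfusion condition, and its cut-off is set by the same unmasked voxels. Under the assumed values, unmasked Dice with the truly hypoxic voxels runs from about 0 (R2' near that of normal tissue, or noisy CBV) to above 0.9 (R2' near 0 and low noise). A CBV floor brings it to about 0.8-1.0 where hypoxic tissue has normal CBV, and to 0.33-0.68 in the harsher mix. A floor does not cure loss from noise in R2' itself.

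A reader might infer that necrosis, cavity and oedema will become the BOLD HTV and that BOLD must fail. The documents do not support that: they give no R2', CBV or noise values, oedema matters only if its CBV is low, and inclusion of the cavity is not stated. Nor do they support saying that the PET HTV is spoiled, or that CBF > 0 excludes nothing. The weak CBF condition is a second, smaller fault that bears mainly on OE. The sample size is unaffected.

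**What to change.** Before any HTV is computed, pre-specify one perfusion mask per scan:

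1. Replace CBF > 0 by CBF and CBV above the DSC noise floor, or above a fixed fraction of contralateral normal-appearing white matter.
2. Apply the same mask to the OE, BOLD and PET HTVs. For BOLD, apply it before the rOEF mean and SD are calculated; masking afterwards leaves the cut-off inflated.
3. State that resection cavity, CSF and visible necrosis are excluded from the ROI.
4. Report one alternative floor as a sensitivity analysis.

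The cost is wording and a little analysis time: the CBF and CBV maps and a contralateral reference region are already planned. The drawback is that some poorly perfused but viable hypoxic voxels are lost, which the plan already accepts for OE and PET. Fixing the floor in advance matters because one chosen after seeing the Dice values would be data-driven.
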